## Abstract

**Background:**

The median laparotomy is frequently used by abdominal surgeons to gain rapid and wide access to the abdominal cavity with minimal damage to nerves, vascular structures and muscles of the abdominal wall. However, incisional hernia remains the most common complication after median laparotomy, with reported incidences varying between 2-20%. Recent clinical and experimental data showed a continuous suture technique with many small tissue bites in the aponeurosis only, is possibly more effective in the prevention of incisional hernia when compared to the common used large bite technique or mass closure.

**Methods/Design:**

The STITCH trial is a double-blinded multicenter randomized controlled trial designed to compare a standardized large bite technique with a standardized small bites technique. The main objective is to compare both suture techniques for incidence of incisional hernia after one year. Secondary outcomes will include postoperative complications, direct costs, indirect costs and quality of life.

A total of 576 patients will be randomized between a standardized small bites or large bites technique. At least 10 departments of general surgery and two departments of oncological gynaecology will participate in this trial. Both techniques have a standardized amount of stitches per cm wound length and suture length wound length ratio's are calculated in each patient. Follow up will be at 1 month for wound infection and 1 year for incisional hernia. Ultrasound examinations will be performed at both time points to measure the distance between the rectus muscles (at 3 points) and to objectify presence or absence of incisional hernia. Patients, investigators and radiologists will be blinded during follow up, although the surgeon can not be blinded during the surgical procedure.

**Conclusion:**

The STITCH trial will provide level 1b evidence to support the preference for either a continuous suture technique with many small tissue bites in the aponeurosis only or for the commonly used large bites technique.

**Trial registration:**

Clinicaltrials.gov NCT01132209

## Background

The median laparotomy is frequently used by abdominal surgeons to gain rapid and wide access to the abdominal cavity with minimal damage to nerves, vascular structures and muscles of the abdominal wall. However, incisional hernia remains the most common complication after median laparotomy, with reported incidences varying between 2-20%[1-5]. Even higher incidences up to 30-35% have been reported in obese and aortic aneurysm patients [6-10]. Incisional hernia can cause discomfort, impair quality of life or result in serious life-threatening conditions, such as incarceration or strangulation of the bowel [5]. Median laparotomies and incisional hernias have been subject of investigation for a long period of time already. Although a lot is known about patient related risk factors and suture materials, technical risk factors such as suture techniques have not been investigated thoroughly [5,11,12].

For prevention of incisional hernia, many clinical trials and meta-analyses have demonstrated that a mass closure technique with a simple running suture is the best option to close a midline incision. A mass closure technique with a running suture is also easier and quicker to perform than layered techniques with interrupted sutures [5,12-14]. Furthermore, the use of slowly resorbable suture material compared with non-resorbable suture material decreases the incidence of incisional hernia, and it also lowers the incidence and intensity of postoperative pain and wound infection [12,15,16].

### Suture length to wound length ratio and small bites

Several authors have stated that a suture length to wound length ratio (SL:WL) of four or more must be achieved, since a lower ratio is associated with an increased rate of incisional hernia [7,17-20]. It has often been recommended to place continuous stitches more than 10 mm from the wound edge in combination with a long stitch length [19,21-28]. A long stitch is the result of a large bite with the largest portion of fascia possible, aiming to increase tensile strength and to decrease the risk of fascial dehiscence. However, long stitches have been associated with high rates of both wound infection and incisional hernia [17,29,30]. A long stitch length may be associated with higher risks of wound infection due to an increase in the amount of necrotic tissue within the wound. In experimental studies, the long stitch length has been found to compress or cut through soft tissue included in the stitch [31,32]. The risk of incisional hernia may be higher because the stitch tends to slacken, which allows wound edges to separate.

Small stitches, placed 4-6 mm from the wound edge, only cut through the aponeurosis and not through the rectus abdominis muscle. Recent experimental data show that the small bites technique results in stronger wounds and faster healing than the routine large bite technique [33]. Our experiments in a porcine model showed a 47% increase in breaking strength when small bites were used compared to the routine technique [32]. A recent randomized of randomised clinical study by Millbourn et al. reported a decrease of incidence of incisional hernia of 70% 18% to 5.6%, p < 0.001) and a decrease of 50%, (10.2% to 5.2%, p = 0.020) of wound infection [34]. These results are very promising with regard to the prevention of incisional hernia and wound infection. The benefits of this technique need to be confirmed in a multicenter double-blinded randomized controlled trial.

In daily practice, most surgeons in the Netherlands use the large bite technique with large suture distances. With large bites, SL:WL ratio depends on the thickness of the abdominal wall including the muscles, the bite size, the number of stitches and the traction on the sutures during suturing. With large bites, an unanswered question remains with regard to how the SL:WL ratio of 4 should be reached. With a low traction force, fewer stitches are needed, but the slacking effect during the postoperative period may influence results.

With small stitches, SL:WL ratio is mostly dependent on the number of stitches. There is no sufficient evidence to prefer one suture closure technique over the other in order to prevent incisional hernia and fascia dehiscence.

### Objective

The objective of the STITCH trial (Suture Techniques to reduce the Incidence of The inCisional Hernia) is to compare the small bites technique decribed by Millbourn et al. with a standardized large bites technique.

The overall objective of the study is reduction of the incidence of the most frequent complication of abdominal surgery, i.e., incisional hernia. We hypothesize that the small bites technique will result in a significant reduction of the incidence of incisional hernia, which may lead to a reduced morbidity and a better quality of life for patients and a significant reduction of costs.

Primary endpoint will be incisional hernia occurrence within one year after surgery, either clinically and/or ultrasonographically detected. Secondary endpoints include postoperative complications, in particular surgical site infection, burst abdomen and wound pain in the first postoperative month.

## Methods/Design

### Trial Design

The STITCH trial has been designed as a prospective, multicenter, double-blind, randomized controlled trial, in which the large bites technique will be compared with the small bites technique.

### Participants

Patients scheduled for an elective abdominal operation through a midline incision will be asked for informed consent at the outpatient clinic or in hospital on the day preceding the day of surgery. Also, emergency laparotomies can be included in this trial if the patient is able to sign the informed consent. We intend to investigate the efficacy of the small bites technique in all risk groups. This also includes oncological gynaecological patients in centers with at least 50 median laparotomies a year.

#### Inclusion criteria

• Signed informed consent

• Laparotomy through a midline incision

• Age 18 years or older

#### Exclusion criteria

• Previous incisional hernia or fascial dehiscence with secondary healing after a midline incision

• Abdominal surgery through a midline incision within the last three months

• Pregnancy

Since the STITCH trial is an intervention study, it is not considered desirable to combine this trial with other intervention studies. In case of non-intervention (registration) studies, it will be judged on individual basis whether it is suitable and ethically correct to include a patient in both the STITCH trial and in another study. Patients will be included in the STITCH trial in combination with one other trial (registration trials only), provided that it is possible to organize the informed consent and the follow up in a proper way for the individual patient for both trials.

### Registration procedure

Included patient are registrated before surgery in an online data base (designed and managed by HOVON data center, Rotterdam, the Netherlands,) after signed informed consent via the Internet via TOP (Trial Online Process; see http://www.stitchtrial.nl). The patient namecode, date of birth, name of caller, name of responsible physician, sex and eligible criteria will be registered. Every participating institution has its own login code.

### Randomisation procedure

The randomization process is started only 15 minutes before closure to prevent consequences due to the trial during the operation with the online TOP randomisation.

Patients will be randomized between closure with the large tissue bites technique or with the small tissue bites technique. Randomisation is stratified by center, and between surgeon or resident with a minimization procedure, ensuring balance within each stratum and overall balance. The randomization result will be given immediately by TOP. A confirmation email without randomization result will be send to the investigator.

Patients will be kept unaware of the type of closure until the endpoint of the trial. Surgeons or residents blinded for the procedure will perform out patient clinic controls. Postoperative ultrasonography will be performed by radiologists blinded for type of closure. The randomisation procedure, blinding and objectification of incisional hernia by ultrasound will provide the best possible data to support preference for the large bites technique or the small bites technique over the other for closure of the abdominal wall.

### Interventions

In this trial the large bites technique will be compared with the small tissue bites technique as developed in Sundsvall Hospital, Sweden [18]. In the first group, the conventional large bites technique will be applied with bite widths of 1 cm and intersuture spacing of 1 cm with the use of one PDS plus II loop with a 48 mm needle. In the second group, the small bites technique will be applied with bite widths of 0,5 cm and intersuture spacing of 0,5 cm with the use of PDS plus II 2-0 with a 31 mm needle. In the small bites technique, twice as many stitches will be placed per sutured cm, with a smaller needle and thinner suture material. In the Swedish hospital where the small bites techniques has been in use for many years, this combination proved the easiest and safest method to perform the small bites technique [18,34].

In both groups wound length is measured before closing of the fascia. After measument of the woundlength, the number of stitches is calculated. In the large bites technique at least one suture per cm wound length must be placed. In the small bites technique at least two sutures per cm wound length must be placed. The number of stitches is counted by the assistant during closure.

In both arms, suturing is initiated at both ends of the incision towards the middle where an overlap will be created of at least 2 cm. The remaining sutures will be measured and the suture length used for closure of the fascia and the SL:WL ratio will be calculated by the scrub nurse. In both arms, suture length to wound length ratios (SL:WL) of 4:1 are aimed at.

### Implementation

In every hospital the OR nurses the surgeons or gynecologists and residents are instructed before the start of the trial in the individual institution during presentations and demonstration movies. During at least the first five inclusions the study coordinator will be present in the OR before randomization to assist randomization and control the correct applying of the standardized techniques. For every included patient a form with the detailed closing protocol is added to the clinical chart. Only when the surgeon is familiar with both the techniques, the nurses with the counting and measuring of the stitches and suture material and the study, centers are allowed to run the trial. Also, for every included patient a form with the detailed closing protocol is added to the clinical chart. During the study unplanned audits are performed to control quality.

#### Outcome parameters

##### Primary outcome

• Primary outcome will be incisional hernia occurrence within one year after surgery, either clinically and/or ultrasonographically detected.

##### Secondary outcome

• Postoperative complications

• Pain

• Quality of life

• Cost effectiveness

We use the definition of the incisional hernia by the European Hernia Society: 'any abdominal wall gap with or without bulge in the area of a postoperative scar perceptible or palpable by clinical examination or imaging'. The classification made by the European Hernia Society is used [35]. The classification of incisional hernias: Incisional hernias will be classified according to their localization, size, reducibility and symptoms.

Discharge dates and complications will be registered. Patients who fail to keep their annual clinic appointment will be given the option of a further appointment at a more suitable date or a visit to their home if they cannot make it to the outpatient clinic. The following data will be gathered at different points in time:

##### Preoperative data

• Date of birth

• Length and weight

• Current smoker (Yes or No)

• Medical history (including chronic obstructive pulmonary disease (COPD), diabetes mellitus, cardiac disease, prior laparotomies)

• Preoperative radiotherapy or chemotherapy

• Preoperative or perioperative corticosteroids

• Previous abdominal operations

• Other abdominal wall hernias

• American Society of Anaesthesiologists (ASA) classification

• Width of linea alba (if preoperative Computed Tomography Imaging is available)

### Operation data

• Type of operation

• Suture length: wound length ratio

• Number of stitches

• Length of incision

• Closure time

• Blood loss

• Operation time

• Antibiotic prophylaxis

• Drains and location

• Thrombosis prophylaxis

• Pain medication

• Peroperative complications (intestinal lesions, bleeding, other)

• Epidural catheter

#### Postoperative data

• Blood transfusion

• Postoperative ventilation and duration

• Postoperative corticosteroids

• Postoperative radiation therapy

• Postoperative pain medication

• Postoperative ileus and duration

• Postoperative complications:

○ Centers for Disease Control criteria for Surgical Site Infection, according to the guidelines proposed by Mangram in 1999 [36] Appendix 1.

○ Wound haematoma: accumulation of blood in the wound area, which warrants surgical exploration and intervention.

○ Pulmonary infections

○ Ventilation problems

○ Re-admission and indication

○ VAS pain score until day 6 post operative

At 1 and 12 months, ultrasound imaging will be performed to examine the midline for any asymptomatic clinically not detectable incisional hernias. Size and location of any incisional hernias will be registered.

### Outpatient clinic follow up

• Outpatient clinic visit at 1 and 12 months

○ Incisional hernia

○ Wound infection

○ Seroma formation

○ Other wound problems

○ Other abdominal wall hernia

• Ultrasound at 1 and 12 months

• VAS pain scores and Quality of Life forms preoperatively (day of operation or the day before) and at 1,3, 6 and 12 months

#### Ultrasound examinations

During the 1 month and 1 year follow up an ultra sound examination will be performed to measure the distance between the rectus muscles at 3 point in the incision and check for incisional hernia. A specific score is used for the ultrasound examination. At ten points, which include 4 measurements of the distance between the rectus muscle, the quality of the scar in the abdominal wall is objectified. With this method the conclusion if there is an incisional hernia can also be made on the score list. In this list is controlled for:

An intact linea alba?

Bulging without Valsalva manouvre?

Bulging with Valsalva manouvre?

Distance between rectus muscles in scar on 1/3 cranial part in cm?

Distance between rectus muscles in scar on 1/3 caudal part in cm?

Maximum distance between rectus muscles in scar in cm?

Maximum distance between rectus muscles at place of bulging or defect in cm?

Is there a defect? If yes, the size of the defect and location

Is there fatty tissue in the defect?

Is there a bowel loop in the defect?

The radiologist is asked to make prints of every measurement and finding.

Quality of life will be assessed based on standardized Quality of Life forms including the EuroQol-5D and Short Form-36 before and at 1 month, 3 months, 6 months, and 12 months after surgery.

#### Economic evaluation

We will perform an ex-post economic evaluation in which a new suture technique using small bites is compared with the traditionally applied large bites technique, from a societal perspective. The economic evaluation will be performed in accordance with Dutch guidelines (Oostenbrink, 2004).

To measure the economic impact of the new suture technique using small bites the cost-effectiveness will be assessed by calculating the incremental cost-effectiveness ratio, defined here as the difference in average costs between both suture techniques divided by the difference in average effects. The primary outcome measure will be the costs per reduced incisional hernia within 1 year. Secondary, a cost-utility analysis will be performed using costs per quality adjusted life year (QALY) as outcome measure, using the EQ-5D.

Costs for all separate actions and time used by all individual health care professionals, and all other materials will be measured from a societal perspective for both bites techniques, which means that both direct medical costs (e.g. intervention costs, intramural and extramural medical costs) and indirect costs (absence from work, patient costs) will be included in the analysis.

For the most important cost items, unit prices will be determined by following the micro-costing method (Gold et al, 1996), which is based on a detailed inventory and measurement of all resources used. Resource costs arise within the hospital and consist of outpatient visits, inpatient days, use of the operation room, radiology examinations, blood tests, etc. Real medical costs will be calculated by multiplying the volumes of health care use with the corresponding unit prices. For instance, the calculation of the costs of both suture techniques will consist of detailed measurement of investments in manpower, equipment, materials, housing and overhead. The salary schemes of hospitals and other health care suppliers will be used to estimate costs per hour for each health care professional. Taxes, social securities and vacations will be included.

Data on effects (reduction of incisional hernia), costs (time costs of new suture technique and material and development costs) and savings (reduced health care use of patients without incisional hernia) will all be collected in this study. Data on treatment (hospitalisation) and follow-up consultations will be collected retrospectively from (electronic) patient charts and hospital administration. This data will be collected by health care professionals using a data-collection form. Information will collected on:

- length of hospital stay

- length of stay in ICU

- reinterventions

Data on extramural care, work absence and other patient costs will be gathered via questionnaires at each follow-up (1 and 12 months).

For a description of the calculation of the effect measures see paragraph 'outcome parameters'.

Discounting of future costs and effects is not relevant because of the limited time horizon of 1 year. When costs of a treatment are similar across subgroups, the absolute benefit determines the cost-effectiveness of a treatment for a specific subgroup.

Randomized controlled trials are designed to evaluate the effects of treatment at the group level, and cost-effectiveness is usually calculated for this group as a whole. There could however be substantial and relevant between subgroup variability. It is therefore common to consider subgroup specific effects of interventions. The subgroup specific cost-effectiveness will be estimated by first deriving a prognostic index, based on the predefined predictors of incisional hernia: abdominal aneurysm aorta (AAA), obesity, diabetes, COPD, corticosteroid usage, radiotherapy, cardiovascular disease, smoking, age, cancer, other abdominal wall hernias and collagen disorders.

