### Sample size calculation

Millbourn et al. found a decrease in the incidence of incisional hernia from 18% to 5,6% in a randomized controlled trial [34]. In this trial, follow-up consisted of clinical instead of radiological examination for incisional hernia occurrence. In this trial, ultrasound examination will be used in order to be able to diagnose incisional hernia with higher sensitivity. It is expected that a relative decrease of the incidence incisional hernia after one year of 50% is reasonable. The mean reported one year incidence of incisional hernia in literature is 15%[1-5]. In order to reduce the mean incidence of incisional hernia from 15 to 7.5%, power calculations showed that two groups of 259 evaluable patients each are needed (power = 0.80, alfa = 0.05). Loss to follow-up is estimated at 10% of included patients. A total of 576 patients (2 × 288) will be included in the study to correct for loss to follow-up. Overall effects will be calculated adjusted for predictive baseline characteristics, which will lead to a higher statistical power.

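### The cost-utility analysis does not bring the preoperative EQ-5D into the QALY comparison, which forgoes precision that is free to obtain

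*Protocol article*

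**What the plan says.** The Economic evaluation section gives one definition of the cost-effectiveness ratio, "defined here as the difference in average costs between both suture techniques divided by the difference in average effects". It then applies that definition twice. The primary economic measure is cost per hernia avoided: "The primary outcome measure will be the costs per reduced incisional hernia within 1 year". The cost-utility analysis comes second: "Secondary, a cost-utility analysis will be performed using costs per quality adjusted life year (QALY) as outcome measure, using the EQ-5D". For the calculation of effect measures the section points to the outcome parameters, where no QALY calculation is given.

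The preoperative EQ-5D is collected. Ultrasound examinations lists the quality-of-life forms as "including the EuroQol-5D and Short Form-36 before and at 1 month, 3 months, 6 months, and 12 months after surgery", and Outpatient clinic follow up fixes the first one: "VAS pain scores and Quality of Life forms preoperatively (day of operation or the day before) and at 1,3, 6 and 12 months". Under Randomisation procedure, allocation starts only 15 minutes before closure, so the preoperative form precedes it.

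Baseline adjustment is mentioned in two other places:

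- Sample size calculation: "Overall effects will be calculated adjusted for predictive baseline characteristics, which will lead to a higher statistical power". QALYs are not named.
- Statistical analysis: a covariate-adjusted Cox model for hernia, with a list of hernia predictors that does not include the EQ-5D. The similar list in Economic evaluation feeds a prognostic index for subgroup cost-effectiveness and does not include it either.

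Statistical analysis also plans paired t-tests of baseline against follow-up and repeated measures analysis for the quality-of-life data. Neither is linked to the QALY difference.

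**The concern.** A patient's preoperative utility is normally among the strongest available predictors of that patient's QALYs over the following year. The trial records it before allocation, yet the only estimator given for the QALY effect is a difference in averages that makes no mention of it. Allocation is balanced by centre and by surgeon or resident, not by health state. The population includes elective, emergency and gynaecological oncology patients, so a wide spread of preoperative utility is plausible.

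Two things are at stake. The interval around the QALY difference may be wider than the data require. And a chance difference in preoperative EQ-5D between arms will move the QALY estimate, and with it the cost per QALY, for reasons unrelated to suture technique. If adjustment is decided only after the imbalance has been seen, the choice is open to question.

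**Working it through.** **Plan's own figures.** The article has no sample size, standard deviation or power figure for QALYs. Its only sample size is for hernia, 15% against 7.5%. A log-rank calculation reproduces it: hazard ratio ln(0.925)/ln(0.85) = 0.480; events 4(1.960 + 0.842)²/ln(0.480)² = 58.2; 58.2/0.1125 = 517, or 259 per arm; 259/0.90 = 288 per arm, 576 in total. I use it only to set n = 259 per arm.

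**Assumptions (not in the documents).** The QALY is the trapezoidal area under the EQ-5D utilities; utility SD is 0.25 at every visit; baseline correlates r_b with each follow-up utility; follow-up utilities correlate r_f with each other.

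**Weights.** For visits at 0, 1, 3, 6 and 12 months the trapezoidal weights are 1/24, 3/24, 5/24, 9/24 and 6/24. The baseline weight is w0 = 1/24, the follow-up weights sum to W = 23/24, and their squares sum to S = (9 + 25 + 81 + 36)/576 = 0.262.

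**Formulas.**

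- Variance factor: V = w0² + 2·w0·r_b·W + r_f·W² + (1 − r_f)·S
- Slope of QALY on baseline: b = w0 + r_b·W
- Squared correlation of QALY with baseline: R² = b²/V
- Unadjusted SE of the QALY difference: 0.25·√V·√(2/259); adjusted SE: the same times √(1 − R²)
- SE of the baseline difference: 0.25·√(2/259) = 0.022; the QALY shift from an imbalance of that size is b × 0.022

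**Worked case, r_b = r_f = 0.5.** V = 0.632; b = 0.0417 + 0.5 × 0.9583 = 0.521; R² = 0.521²/0.632 = 0.43; √(1 − 0.43) = 0.755, so the interval is 24% narrower.

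**Worked case, r_b = 0.2, r_f = 0.6.** V = 0.0017 + 0.0160 + 0.5510 + 0.1049 = 0.674; b = 0.0417 + 0.2 × 0.9583 = 0.233; R² = 0.0544/0.674 = 0.08; √(1 − 0.08) = 0.959, so the interval is 4% narrower.

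| r_b | r_f | R² | Interval narrower by | SE unadjusted to adjusted | Shift per one-SE imbalance |
|---|---|---|---|---|---|
| 0.2 | 0.6 | 0.08 | 4% | 0.0180 to 0.0173 | 0.005 |
| 0.3 | 0.6 | 0.16 | 8% | 0.0181 to 0.0166 | 0.007 |
| 0.3 | 0.3 | 0.22 | 12% | 0.0153 to 0.0135 | 0.007 |
| 0.5 | 0.5 | 0.43 | 24% | 0.0175 to 0.0132 | 0.011 |
| 0.6 | 0.6 | 0.54 | 32% | 0.0185 to 0.0125 | 0.014 |

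The percentage narrowing depends on neither the SD nor n. The last two columns scale with the SD.

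**Route of the shift.** The direct contribution of a 0.022 imbalance is 0.022/24 = 0.0009 QALY. At r = 0.5 the total is 0.011, so nearly all of it comes through the correlation of baseline with later utilities.

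**The case against.** The strongest reply is that the article does not say the QALY difference is raw. The quoted words are a generic definition of the ratio, shared with cost per hernia avoided, and adjusted means would also satisfy them. The sentence in Sample size calculation promises adjustment of overall effects, and the quality-of-life analysis already sets baseline against follow-up. QALY details are often left to a health-economic plan, and this is a condensed article.

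Much of that stands. A reader might infer that the plan has decided against adjustment; the text does not support this, and a fuller document may settle the matter. What remains is that the one estimator stated does not bring in the preoperative EQ-5D. Even if the general adjustment sentence is read to cover QALYs, the covariates the article names are hernia predictors, not baseline utility.

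A reader might also infer bias. Randomisation excludes that: over repeated trials the unadjusted difference is unbiased, and its interval already allows for chance imbalance. Nor can the gain be stated as power, because the article plans no test and no power target for QALYs.

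Lastly, the equal-correlation assumption is favourable. A preoperative form completed on or just before the day of major surgery may predict later utility only weakly. That objection stands, and it is why the range begins at 4%.

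**Conclusion.** The point holds as a modest improvement. The QALY effect is defined only as a difference in averages, and no part of the article uses the preoperative EQ-5D in that comparison. Adjustment would narrow the interval by about 4% if baseline correlates 0.2 with follow-up (and follow-up visits 0.6 with each other), and by 24-32% if all visits correlate equally at 0.5-0.6. With an assumed utility SD of 0.25 and 259 per arm, an ordinary one-SE baseline imbalance would shift the unadjusted QALY difference by about 0.005 to 0.014 across the same range. All these sizes rest on assumed correlations and a trapezoidal QALY; for any positive correlation the direction does not change.

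The primary endpoint, the hernia analysis and the primary economic measure are not affected.

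**What to change.** In Economic evaluation, state that the QALY difference in the cost-utility ratio is the arm coefficient from a linear regression of each patient's 12-month QALY on arm and preoperative EQ-5D utility. Use the same adjusted estimate within whatever interval method is chosen, and report the unadjusted difference alongside. If a separate health-economic plan already says this, a reference to it is enough.

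The cost is a sentence or two of text, one regression in place of a difference in means, and a simple rule for the few patients whose preoperative EQ-5D is missing. No new data, visits or patients are needed.

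### Patient-reported costs are collected only at 1 and 12 months, so 11 of the 12 months rest on one form, although the same patients already complete forms at 3 and 6 months

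*Protocol article*

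**What the plan says.** The Economic evaluation section adopts a societal perspective and commits to counting more than hospital resources: "indirect costs (absence from work, patient costs) will be included in the analysis". The horizon is one year: "Discounting of future costs and effects is not relevant because of the limited time horizon of 1 year".

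Two data sources are named. Hospital treatment and follow-up consultations "will be collected retrospectively from (electronic) patient charts and hospital administration". For the remaining items the source is the patient: "Data on extramural care, work absence and other patient costs will be gathered via questionnaires at each follow-up (1 and 12 months". No recall window, diary or registry is given for them.

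Those two dates match the clinic schedule under Outpatient clinic follow up: "Outpatient clinic visit at 1 and 12 months". The same list has a denser schedule for other patient-completed material: "VAS pain scores and Quality of Life forms preoperatively (day of operation or the day before) and at 1,3, 6 and 12 months". The section on ultrasound examinations repeats this for the EuroQol-5D and Short Form-36: "before and at 1 month, 3 months, 6 months, and 12 months after surgery".

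**The concern.** Care outside the hospital, absence from work and patient costs are what separates a societal analysis from a hospital one. The article expects savings from lower use of care by patients who do not develop a hernia. Any such use or absence arising after the first month falls in the long stretch between the two cost forms, where it is seen once, at the end.

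The schedule is stated outright, so this is not a detail that a condensed article leaves to a fuller document. Nor can an analysis plan repair it, since items not asked at 3 and 6 months cannot be recovered. At stake are the precision and completeness of the patient-reported part of the cost difference, which enters both the cost per hernia avoided and the cost per QALY. A patient lost between the two forms contributes nothing on these items after month 1.

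**Working it through.** **Inputs.** Cost forms at 1 and 12 months, and horizon 12 months (Economic evaluation). Quality-of-life forms at 1, 3, 6 and 12 months (Outpatient clinic follow up; Ultrasound examinations). 259 evaluable patients per arm, 10% loss, 576 in total (Sample size calculation).

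**Step 1: intervals between forms**, counted from surgery at month 0.

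| Schedule | Intervals (months) | Longest | Share of horizon |
|---|---|---|---|
| As written: 1, 12 | 1, 11 | 11 | 11/12 = 92% |
| With existing form dates: 1, 3, 6, 12 | 1, 2, 3, 6 | 6 | 6/12 = 50% |

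**Step 2: what the long interval implies.** If the 12-month form asks about the last *w* months, with *w* at most 11, then 11 − *w* months are not observed. With *w* = 11 nothing is uncovered, but recall is 11 months. As illustrations, *w* = 6 leaves 5 months uncovered and *w* = 3 leaves 8. The two weaknesses trade off, and their sum stays at 11 months. With cost items on all four forms, the same sum for the longest interval is 6 months.

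**Step 3: effect on the comparison.** Let *D* be the true between-arm difference in these items over months 1 to 12, and suppose a fraction *u* of the use goes unreported equally in both arms. The expected measured difference is (1 − *u*)*D*. The article gives no value for *u*, and I assume none. The result shows only that under-reporting at an equal rate shrinks the difference towards zero without changing its sign. Cost components taken from charts are not multiplied by this factor.

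**Step 4: loss to follow-up.** The plan's figure reproduces: 259/(1 − 0.10) = 287.8, rounded up to 288 per arm, and 2 × 288 = 576. The expected loss is 0.10 × 576 = 57.6, about 58 patients (equally, 576 − 2 × 259 = 58). All 58 would lack patient-reported costs after month 1 only if every loss fell after the 1-month form and none returned the 12-month form. The article gives no timing of losses, so 58 is a ceiling at the planned rate.

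**Step 5: what extra forms recover.** A patient lost before month 3 gains nothing. One lost between the 3- and 6-month forms gains 3 − 1 = 2 months of data. One lost between the 6- and 12-month forms gains 6 − 1 = 5 months.

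**The case against.** The strongest reply is that nothing here is an error. Tying cost questionnaires to the two clinic visits is coherent, the evaluation is a secondary outcome, and much of the cost (hospital and ICU stay, reinterventions, consultations) comes from charts. All of that stands, and it limits the point to the questionnaire items and to the rank of an improvement. The offer of another appointment or a home visit to patients who miss the annual visit (Secondary outcome section) also stands. It should reduce missing 12-month forms, though it does not shorten the period they cover.

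A reader might infer more than the article supports:

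- *That an 11-month recall is forced.* It is inferred from the dates, since no window is stated. A shorter window avoids it, at the price of uncovered months.
- *That the cost-effectiveness ratio is biased towards one technique.* Patients are kept unaware of their closure (Randomisation procedure) and both arms have the same schedule, so differential recall is not expected. The article gives nothing from which to size any error.
- *That work absence clusters early and is therefore misplaced.* The article does not say so, and month 1 has its own form.
- *That costs and QALYs on different dates are a defect.* Costs are totals over a period, while QALYs are built from values at time points. The dates need not agree.
- *That some 58 patients would have cost data for only one month.* Chart-based costs do not depend on a returned form.

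The remedy is also partial: half the horizon would still rest on the final form.

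**Conclusion.** The point holds as a cheap, low-priority improvement to the secondary economic evaluation. For extramural care, work absence and other patient costs, one form at month 12 carries 92% of the horizon, through long recall, uncovered months or a mixture of the two. The likely consequence is added noise and some dilution of the between-arm difference in these items. That rests on two assumptions: that recall mainly omits use, and that it does so about equally in both blinded arms. The number of patients without these data after month 1 is at most about 58 of 576, if losses run at the planned 10%. The size of any effect on the cost-effectiveness ratios cannot be given from the article. The trial's primary comparison does not depend on this point.

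**What to change.** Add the items on extramural care, work absence and patient costs to the quality-of-life forms already scheduled at 3 and 6 months. State on every cost form, including the one at 12 months, that it covers the period since the previous form. Build the yearly total from the four periods, and use the 3- and 6-month answers to support imputation for patients lost before month 12.

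The cost is a short extra section on two existing forms, with slightly more patient burden and data entry. The added dates need no new clinic visit if the cost items travel with forms that patients already complete; the article does not say how those forms are delivered, so this should be confirmed. Randomisation, blinding and the hernia assessments are unchanged. A 6-month recall remains between the last two forms.
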